## Abstract

**Background:**

An antifibrinolytic agent that blocks lysine-binding sites on plasminogen molecules, tranexamic acid reduces bleeding-related mortality in women with postpartum hemorrhage (PPH), especially administered fairly soon after delivery. According to the randomized controlled trials thus far reported for PPH prevention after cesarean deliveries (*n* = 16), women who received tranexamic acid had significantly less postpartum blood loss and no increase in severe adverse effects. These were, however, primarily small single-center studies that had fundamental methodological flaws. Multicenter randomized controlled trials with adequate power are necessary to demonstrate its value persuasively before tranexamic acid goes into widespread use for the prevention of PPH after cesarean deliveries.

**Methods/design:**

This study will be a multicenter, double-blind, randomized controlled trial with two parallel groups including 4524 women with cesarean deliveries before or during labor, at a term ≥34 weeks, modeled on our previous study of tranexamic acid administered after vaginal deliveries. Treatment (either tranexamic acid 1 g or placebo) will be administered intravenously just after birth. All women will also receive a prophylactic uterotonic agent. The primary outcome will be the incidence of PPH, defined by a calculated estimated blood loss > 1000 mL or a red blood cell transfusion before day 2 postpartum. This study will have 80% power to show a 20% reduction in the incidence of PPH, from 15.0 to 12.0%.

**Discussion:**

As an, inexpensive, easy to administer drug that can be add to the routine management of cesarean births in delivery rooms, tranexamic acid is a promising candidate for preventing PPH after these births. This large, adequately powered, multicenter randomized placebo-controlled trial seeks to determine if the benefits of the routine prophylactic use of tranexamic acid after cesarean delivery significantly outweigh its risks.

**Trial registration:**

ClinicalTrials.gov NCT03431805 (February 12, 2018).

## Background

### Rationale

#### Prevention of postpartum hemorrhage

The standard definition of a primary postpartum hemorrhage (PPH) is a blood loss of 500 mL or more in the first 24 h after childbirth, regardless of mode of delivery. It causes around 25% of all maternal deaths worldwide [1–3]. Some historical studies have reported that mean blood loss is significantly higher after cesarean than vaginal deliveries [2]. A prospective observational study in France reached a similar conclusion [4]: blood loss > 500 mL occurred in 46.8% of cesarean deliveries and > 1000 mL in 11.6%; the 95th percentile of the volume of blood loss distribution was 1300 mL [4]. Because the authors estimated blood loss mainly by the volume in the suction container from the placental delivery, these data may underestimate the true blood loss. Nonetheless, these estimates of blood loss during cesareans [4] are consistent with those reported by Sheehan et al. in their double-blind randomized controlled trial (RCT) comparing two regimens of prophylactic oxytocin at elective cesarean deliveries (*n* = 2069 in total) [5]. A calculated estimated blood loss ≥1000 mL [calculated estimated blood loss = estimated blood volume × (preoperative hematocrit – postoperative hematocrit/preoperative hematocrit (where estimated blood volume = booking weight (kg) × 85)] defined the PPH incidence that was the primary outcome in their trial. They chose this validated calculation as a quantitative objective measure to estimate blood loss [6, 7] because it is widely accepted that clinicians underestimate this loss [8, 9] and that gravimetric methods include liquor in addition to blood, which limits their accuracy, especially for cesareans [10]. They reported a calculated blood loss ≥1000 mL in around 16% in both groups of women with an elective cesarean [5]. This result is consistent with that of the French prospective study mentioned above, which estimated blood loss clinically [4].

Today, of the components of the active management of the third stage of labor, a package intended to reduce PPH, only one — the administration of a uterotonic agent — has been demonstrated to reduce the incidence of PPH by 50% [2, 3, 11].

#### Tranexamic acid

Tranexamic acid, as an antifibrinolytic agent, blocks lysine-binding sites on plasminogen molecules [12]. It reduces bleeding in elective surgery [13, 14] and mortality in trauma patients [15] and does so without any rise in the number of vascular occlusive events [13–15]. In gynecology, tranexamic acid reduces menstrual blood loss in women with menorrhagia compared with control agents or placebo [16].

In obstetrics, tranexamic acid reduces bleeding-related mortality in women with PPH, especially when administered fairly soon after delivery [17]. The WOMAN trial enrolled 20,060 women with PPH, randomly assigned them to receive tranexamic acid (*n* = 10,051) or placebo (*n* = 10,009), and included 10,036 and 9985, respectively, in the analysis [17]. Significantly fewer women treated with tranexamic acid (1.5% vs 1.9%, risk ratio (RR) 0.81, 95% confidence interval (CI) 0.65–1.00; *P* = 0.045) died due to bleeding, especially those treated within 3 h of delivery (1.2 and 1.7%, respectively, RR 0.69, 95% CI 0.52–0.91; *P* = 0.008). The groups did not differ significantly for adverse (including thromboembolic) events [17]. This team also conducted an individual data meta-analysis that showed a 10% decrease in the survival benefit of tranexamic acid associated with every 15 min delay in treatment administration during the first 3 h; after 3 h, the benefit vanished [18].

##### For prevention of postpartum hemorrhage

We searched Medline through January 1, 2019, and found 20 RCTs aimed at evaluating the preventive impact on PPH of tranexamic acid administered after delivery in addition to prophylactic uterotonics [19–38]. Only four enrolled women with vaginal deliveries [19–22], the sixteen others including women with cesarean delivery [23–38]. Except for the French Tranexamic Acid for Preventing Postpartum Hemorrhage Following a Vaginal Delivery (TRAAP) trial, which we coordinated and on which this protocol is modeled [22, 39], these RCTs took place in countries with low or middle resources (China, India, Iran, Turkey, Pakistan, and Egypt), had major methodological flaws, and their results could have been affected by their potential for selection, performance, and detection biases. Their findings must therefore be interpreted cautiously, as stressed by several authors [12, 39–45]. The TRAAP trial enrolled 4000 women at standard risk for PPH with a planned vaginal delivery of a singleton live fetus at 35 weeks or more of gestation [22]. The primary outcome — blood loss of at least 500 mL — did not differ significantly between women randomized in the tranexamic acid group and those in the placebo group (RR, 0.83; 95% CI, 0.68 to 1.01; *P* = 0.07).

Sixteen RCTs have thus assessed the effect of tranexamic acid in preventing PPH in women who had elective cesareans; they reported a significantly reduced blood loss in those randomized to receive tranexamic acid, with no effect on the cardinal vital signs or on thrombosis [23–38]. Nevertheless, because of their notable methodologic concerns related to blinding, outcome assessment, and attrition bias, their findings must be considered inconclusive. Furthermore, the external validity of the results observed in middle-income countries appears uncertain, and they lacked adequate power to assess severe adverse events [12, 39–45]. The interpretation of their results thus requires particular caution.

Finally, it is important to emphasize that none of these RCTs included cesarean deliveries during labor [12], when moderate and severe blood loss are both significantly more prevalent than before labor [46].

In conclusion, while tranexamic acid appears promising for the prevention of PPH after cesareans, the results currently available do not yet justify its widespread use. We propose to perform an adequately powered, multicenter, randomized, placebo-controlled trial to determine what effect, if any, systematic tranexamic acid administration after cesarean delivery has on PPH incidence.

Our hypothesis, patterned after that of the TRAAP trial for vaginal deliveries [22, 39], is that administration of a low dose of tranexamic acid (1 g) in the 3 min after cesarean delivery and after prophylactic uterotonic administration, reduces blood loss and the incidence of both PPH and its complications.

#### Objectives

The aim of this study is therefore to compare the effect of the administration of a low dose of tranexamic acid (1 g) in the 3 min after a cesarean delivery with placebo, both in addition to prophylactic uterotonics, in a multicenter randomized, double-blind, placebo-controlled trial with two parallel groups.

The specific object ives, similar to but modified from those for the TRAAP trial for vaginal deliveries [22, 39], are as follows:
To assess the effect of tranexamic acid (1 g) on postpartum blood loss after cesarean delivery
Primary outcome
Incidence of PPH defined by a calculated estimated blood loss > 1000 mL [Calculated estimated blood loss = estimated blood volume × (preoperative hematocrit - postoperative hematocrit)/preoperative hematocrit (where estimated blood volume (mL) = weight (Kg) × 85)] or red blood cell (RBC) transfusion before day 2 (D2) postpartum [5–7]. Preoperative hematocrit will be the most recent hematocrit within 1 week before delivery. Postoperative hematocrit will be measured at D2 (see below).Secondary outcomes
Other outcome measures describing postpartum blood loss, including but not limited to calculated blood loss > 500 mL, > 1500 mL and mean total calculated blood loss, mean gravimetrically estimated blood loss by measuring the suction volume and swab weight until discharge from the post-anesthesia care unit (PACU) (i.e., about 2 h after the end of the cesarean) [23] as well as > 500 mL and > 1000 mL; mean gravimetrically estimated blood loss at the end of the cesarean delivery, mean or median number of units of red blood cells transfused, incidence of postpartum iron perfusion, shock, as well as the outcomes previously considered [22, 39]: provider-assessed clinically significant PPH, proportion of women requiring supplementary uterotonic treatment including sulprostone, incidence of postpartum transfusion, incidence of arterial embolization or emergency surgery for PPH, mean peripartum change in hemoglobin and hematocrit as well as hemoglobin drop > 2 g/dL, transfer to intensive care unit (ICU), or death from any cause.To assess the potential adverse effects of tranexamic acid (1 g) after cesarean delivery:
Hemodynamic parameters, adverse gastrointestinal events, renal, hepatic, and coagulation function, and any venous or arterial thrombosis in the 3 months after delivery (39).To assess women’s satisfaction and psychological status at D2 and D60 [39].

## Methods/design

The methodology and design are very similar to and modified from those of the TRAAP trial for vaginal deliveries [22, 39].

### Recruitment and allocation

The recruitment and allocation, including inclusion and exclusion criteria, are essentially identical to those reported previously [22, 39], modified for a population with cesarean rather than vaginal deliveries.

#### Inclusion criteria

Age ≥ 18 yearsCesarean delivery, either before or during laborGestational age ≥ 34 weeksAvailable venous hematocrit value in the week before the cesareanPrenatal hemoglobin level in the week before the cesarean > 90 g/lSigned informed consent

#### Exclusion criteria

History of venous (deep vein thrombosis and/or pulmonary embolism) or arterial (angina pectoris, myocardial infarction, or stroke) thrombosisHistory of epilepsy or seizureAny known active cardiovascular, renal, or liver disordersAutoimmune diseaseSickle cell diseaseSevere hemorrhagic diseasePlacenta previaAbnormally invasive placenta (placenta accreta/increta/percreta)Abruptio placentaeEclampsia or HELLP (Hemolysis Elevated Liver Low Platelet) syndromeIn utero fetal deathAdministration of low-molecular-weight heparin or antiplatelet agents in the week before deliveryKnown hypersensitivity to tranexamic acid or concentrated hydrochloric acidFailed operative vaginal deliveryPlanned general anesthesiaCesarean delivery for the second twin or second/third triplet(s) after vaginal birth of the first twin.Poor understanding of the French language

Women will receive individual information in late pregnancy about the trial from obstetricians and midwives during prenatal visits or from anesthetists during the systematic anesthesia visit, or both.

Women may be pre-included (receive information and sign consent forms) for cesareans both before and during labor when the investigator considers that the woman is likely to have a cesarean delivery. The aim of pre-inclusion is to facilitate recruitment in the trial, particularly the recruitment of cesareans during labor, which may be decided upon and performed in emergency situations.

Women will be randomized to receive either 1 g of tranexamic acid (Sanofi Aventis, Paris, France; Marketing authorization number: 3400931157618 [1974, RCP rev 06.08.2018]) or placebo (normal saline, Fresenius Kabi, Sèvres, France; Marketing authorization number: 3400941573941, RCP rev 02.01.2018), at a 1:1 ratio. The Clinical Epidemiology Unit (CEU) of the Bordeaux University Hospital will create and securely hold the randomization list for allocations to the tranexamic acid and placebo groups. As in the previous trial [22, 39], a list of treatment units, containing the type of product (tranexamic acid or placebo) and the corresponding treatment number, will be forwarded to the pharmacy department of the Angers University Hospital, a member of the PPRIGO hospital pharmacists’ consortium (Production Pharmaceutique pour la Recherche Institutionnelle du Grand Ouest). The blinded products will be supplied in numbered, labeled boxes, each containing a 10-mL vial of the study drug (1 g of tranexamic acid or placebo according to the randomization list). All boxes and vials will be identically labeled, and the drug packs will be differentiated only by the treatment number. Accordingly, all participants, including caregivers, will be masked and the women’s safety simultaneously guaranteed*.*

The randomization will be centralized and stratified by center and the timing of the cesarean (before or during labor). Randomization numbers will be attributed through a web platform (Ennov Clinical Software). Once a woman has been included and a randomization number assigned to her, she will retain this number even in case of withdrawal from the study.

### Intervention

As in the previous trial [22, 39] the intervention will be the intravenous administration of a 10-mL blinded vial of the study drug (either 1 g of tranexamic acid or placebo, according to the randomization group), slowly (over 30–60 s), in the 3 min after birth, the routine prophylactic uterotonic administration, and cord clamping, all generally by the anesthesiologist or nurse-anesthetist.

Except for the content of the study drug vial, all aspects of management of cesarean delivery, including the third stage, will be identical in both arms as previously reported [22]:
Routine prophylactic intravenous injection of 5 or 10 IU oxytocin or 100 micrograms carbetocin (according to the hospital’s policy) at delivery of the anterior shoulder or in the 3 min after birth, as recommended in the national clinical practice guidelines issued by the French College of Gynecologists and Obstetricians [47].

### Other aspects of the cesarean procedure

Surgeons will be asked to operate with a standardized procedure:
○ Because the Joel-Cohen technique and its variants (Misgav-Ladach technique) have been associated with less blood loss than the use of the Pfannenstiel abdominal incision (and its variants), use of the former techniques will be preferred [48, 49].○ Because delivery of the placenta with cord traction at cesarean section has been associated with less blood loss than manual removal, cord traction will be preferred in the absence of severe bleeding [50].The care providers will decide upon the administration of additional uterotonics and the management of PPH, in a manner consistent with French guidelines [47] and the center’s protocol. In particular, the use of tranexamic acid for the treatment of PPH will be allowed and left to the practitioner’s discretion according to the center’s protocol.The method for estimating blood loss will be standardized and include:
○ Recording of the suction blood volume.○ Weighing of all swabs or material used to measure additional blood loss.Finally, because the obstetrician’s level of experience may affect estimated blood loss during or after a cesarean delivery, the obstetrician’s experience, categorized as junior or senior according to years of specialist training, will be recorded [5].

### Outcome measures

#### Primary outcome measure

The trial’s primary outcome will be the incidence of PPH, defined by a calculated estimated blood loss > 1000 mL or RBC transfusion up to D2 [5]. Calculated estimated blood loss will be based on the difference between the preoperative and postoperative packed cell volume (PCV), also known as hematocrit; it will be calculated as follows [5–7]: calculated estimated blood loss = estimated blood volume × (preoperative hematocrit – postoperative hematocrit/preoperative hematocrit (where estimated blood volume (mL) = weight (kg) × 85).

We have chosen this calculation as a quantitative objective measure to estimate blood loss because of the inaccuracy of blood loss estimation for cesareans through other methods, as described above [2, 8–10].

Preoperative hematocrit will be the most recent hematocrit measured within 1 week before delivery. Postoperative hematocrit will be the hematocrit obtained by blood sampling at D2. If hematocrit is not available at D2, then hematocrit at D3 will be considered; if it is also missing, then the postpartum hematocrit closest to D2 in the absence of transfusion will be considered [39].

All women who receive RBC transfusion for PPH between delivery and D2 postpartum are defined to have PPH and meet the criteria for the primary outcome [5]. Calculated blood loss is impossible to determine for these women. Moreover, women only rarely receive an RBC transfusion for a blood loss less than 1000 mL [2, 4, 6, 47, 51]. As a marker of significant maternal morbidity, RBC transfusion is considered equivalent or superior to blood loss greater than 1000 mL [2, 3, 47, 52].

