#### Laboratory

incidence of calculated blood loss > 500 mL and > 1500 mLmean total calculated blood lossmean peripartum change in hemoglobin (difference between hemoglobin before delivery and at D2) [22, 39]Hemoglobin drop > 2 g/dL (between hemoglobin before delivery and at D2) [22, 39]

For all laboratory indicators, the predelivery reference examination will be the most recent blood count obtained within 1 week before delivery. As previously described [22, 39], all patients included in the trial will provide a blood sample on the second day postpartum (D2) to measure their peripartum hemoglobin and hematocrit and calculate the change in these two indicators. If no blood sample is available from D2, these measurements will be assessed from a D3 blood sample, if available. If no blood sample is available from D2 or D3, they will be assessed from the blood sample closest to D2 in the absence of transfusion.
The occurrence of potential adverse effects of tranexamic acid, most as previously reported (39), with some modifications:

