### Sample size

We assumed a 15% incidence of our primary outcome (calculated blood loss > 1000 mL or RBC transfusion before D2) after cesareans in the absence of tranexamic acid, based on the results from a high-quality RCT conducted in the Republic of Ireland with a similar outcome measure (*n* = 2069) [5]. To show a relative reduction of at least 20% in the incidence of postpartum hemorrhage in the tranexamic acid arm — that is, an incidence of 12% or less in this arm, with α = 0.05, 1 − β = 0.80, and a bilateral test, the study will require 2036 women with a cesarean delivery in each group, totaling 4072 participants. A higher number of randomized women must be included given that some will have a scheduled cesarean cancelled, be lost to follow-up, or lack the postpartum blood sample needed to assess the primary outcome (estimated at a maximum of 10%). Accordingly, we plan to include 2262 women in each group, totaling 4524 participants.

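### Transfused women have no stated rule in the calculated-loss secondary outcomes, although the protocol says their calculated loss cannot be determined

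*Protocol article*

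**What the plan says.** All places are in the protocol article.

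- **Primary outcome measure.** The outcome is calculated loss above 1000 mL or red-cell transfusion up to D2. Of women transfused for hemorrhage in that period the article says "Calculated blood loss is impossible to determine for these women", so they count as having the outcome. It adds that transfusion for a loss under 1000 mL is rare, and treats transfusion as at least equivalent to a loss above 1000 mL.
- **Secondary outcomes, Laboratory.** Five outcomes rest on D2 values: calculated loss above 500 mL, calculated loss above 1500 mL, mean total calculated loss, mean change in hemoglobin, and a hemoglobin drop above 2 g/dL. Every woman gives a D2 sample, and D3 is the first fallback. Only if both are missing does a transfusion condition appear: "they will be assessed from the blood sample closest to D2 in the absence of transfusion".
- **Statistical analysis.** Secondary outcomes are analyzed in the modified intention-to-treat population. Effects are reported as relative risks and absolute risk differences for binary outcomes, and as mean differences for quantitative ones. No transfusion rule is given.

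**The concern.** The calculated-loss formula reads blood loss from the fall in hematocrit. Transfused red cells raise the D2 hematocrit, so the formula understates the loss. The article recognizes this for the primary outcome but then asks for the same quantity three more times.

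Two readings are open. If the D2 value is used because a sample exists, the heaviest bleeds are recorded as smaller than they were. If the value is treated as undeterminable, the woman leaves the analysis because of something that happened after randomization and that treatment may affect. Transfusion is itself listed among the efficacy outcomes. If tranexamic acid works, more of the large placebo bleeds are hidden or removed, and the absolute effects shrink toward zero.

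The two hemoglobin outcomes differ. The D2 value exists and can be compared with the predelivery value, but transfused cells conceal part of the drop.

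**Working it through.** **1. The plan's own figure.** Inputs from Sample size: "We assumed a 15% incidence of our primary outcome", "an incidence of 12% or less in this arm", "with α = 0.05, 1 − β = 0.80, and a bilateral test". With pooled proportion 0.135:

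n = [1.960 × √(2 × 0.135 × 0.865) + 0.842 × √(0.15 × 0.85 + 0.12 × 0.88)]² / 0.03² ≈ 2036 per group.

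This matches "the study will require 2036 women with a cesarean delivery in each group, totaling 4072 participants". Allowing for 10% loss, 2036 / 0.9 = 2262.2, in line with "we plan to include 2262 women in each group, totaling 4524 participants". Transfused women are already events in the primary outcome, so nothing here changes.

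**2. What a post-transfusion D2 value does to one woman.** The article's formula is loss = 85 × weight × (pre − post) / pre. Assumed, not in the document: 75 kg, preoperative hematocrit 36%, and a rise of 2 to 3 hematocrit points per unit.

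- Blood volume is 85 × 75 = 6375 mL, so each restored point hides 6375 / 36 = 177 mL.
- A true loss of 2000 mL gives an untransfused hematocrit of 36 × (1 − 2000/6375) = 24.7%.
- One unit: calculated loss 1469 to 1646 mL.
- Two units: 937 to 1292 mL.
- Four units: −125 to 583 mL.
- Her hemoglobin drop, taken as the hematocrit fall divided by 3, is 3.8 g/dL untransfused, 1.8 to 2.4 g/dL after two units, and −0.2 to 1.1 g/dL after four.

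**3. What it does to the comparison.** The article gives no transfusion rate, so a model is assumed: lognormal loss, placebo median 600 mL, log-scale SD 0.493, treatment multiplier 0.934.

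- Above 1000 mL: ln(1000/600)/0.493 = 1.036 gives 15.0% on placebo; dividing the threshold by 0.934 gives 12.0% on treatment. This matches the design.
- True mean difference: 600 × exp(0.493²/2) × (1 − 0.934) = 677.5 × 0.066 = 44.7 mL.
- Above 1500 mL: 3.15% against 2.29%, so risk difference 0.86 points and relative risk 0.73.

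The probability of transfusion is logistic in true loss, with midpoints 2200, 1800 and 1600 mL and scales 250, 200 and 200 mL. Post-transfusion values assume two units and +6 points, that is 6 × 177 = 1062 mL hidden. Results by numerical integration:

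| Placebo transfused | Mean difference, dropped | Mean difference, post-transfusion value | Placebo incidence > 1500 mL, dropped | Risk difference > 1500 mL, dropped | Relative risk > 1500 mL, dropped |
|---|---|---|---|---|---|
| none affected | 44.7 mL | 44.7 mL | 3.15% | 0.86 points | 0.73 |
| 1.1% | 41.1 mL | 41.7 mL | 2.44% | 0.65 points | 0.73 |
| 2.5% | 38.1 mL | 38.4 mL | 1.64% | 0.43 points | 0.74 |
| 4.5% | 35.6 mL | 34.6 mL | 1.06% | 0.28 points | 0.74 |

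Dropping attenuates the mean difference by 8%, 15% and 20% (for example 1 − 35.6/44.7). The placebo incidence above 1500 mL falls by 23%, 48% and 66% (for example 1 − 1.06/3.15). The relative risk above 500 mL stays at about 0.92.

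**4. Cross-check without the lognormal model.** Suppose 1% to 4% are transfused (41 to 163 of 4072), 50% to 80% of them truly exceed 1500 mL, and other women supply 2 to 3 such events per 100 randomized. The share of true events lost then runs from 0.005/0.035 = 14% to 0.032/0.052 = 62%.

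**The case against.** The best defense is that the primary-outcome section already supplies the rule: calculated loss is undeterminable in transfused women, so it is missing for the secondary outcomes, and handling missing values belongs in an analysis plan that is not shown. A reader may therefore not assert that the post-transfusion value will certainly be used. That stands. But the Laboratory section limits the transfusion condition to the third-choice sample and otherwise takes a D2 value from everyone, so the article's own text points both ways, and neither reading is harmless.

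Three stronger inferences are not supported:

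- **All five laboratory outcomes are undeterminable.** The statement concerns calculated loss, which covers three. The hemoglobin outcomes are masked, not impossible to measure.
- **The treatment effect is badly distorted, or the 1500 mL outcome is emptied.** The loss is in incidence, absolute difference and precision. The relative risk moves only from 0.73 to about 0.74. For the mean difference at 2036 per arm, the expected z falls from about 4.15 to about 4.0 when women are dropped at the highest rate, because removing the tail also cuts the variance. With post-transfusion values it falls further, to about 3.6.
- **Every transfused woman is recorded as a small loss.** That depends on units given. After two units a 2000 mL bleed reads 937 to 1292 mL, still above 500 mL.

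It is also fair that severe bleeding is captured elsewhere, through transfusion incidence, units given, gravimetric loss, embolization or surgery, shock and transfer to intensive care.

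**Conclusion.** The inconsistency is real. It is direct for the three calculated-loss outcomes and indirect, through masking, for the two hemoglobin outcomes. Under assumed placebo transfusion rates of about 1% to 4.5%, the mean difference in calculated loss shrinks by roughly 8% to 20% if transfused women are dropped, and by a similar amount if post-transfusion values are used. The placebo incidence above 1500 mL falls by roughly a quarter to two thirds, and the absolute risk difference falls with it. Relative risks are almost unchanged.

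The primary outcome and its sample size are unaffected. The sizes rest on the assumed loss distribution, transfusion rates and hematocrit rise per unit, none of which the document gives. The direction follows from the formula and from the article's own statement that transfusion seldom follows a loss under 1000 mL. This is a wording-level correction to secondary outcomes, best settled before unblinding because the choice changes the reported absolute effects.

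**What to change.** 1. Apply the transfusion restriction to the D2 and D3 samples as well as to the last fallback, so that no hematocrit or hemoglobin drawn after a red-cell transfusion is used at face value.
2. Count women transfused by D2 as events for calculated loss above 500 mL. This follows from the article's equating transfusion with a loss above 1000 mL.
3. Keep transfused women in the analyses of loss above 1500 mL, mean calculated loss, hemoglobin change and hemoglobin drop above 2 g/dL through a prespecified rule: for example, a pre-transfusion postpartum value where one exists, otherwise worst rank or imputation.
4. Report a sensitivity analysis of loss above 1500 mL or red-cell transfusion, labelled as a separate composite. It should not replace the 1500 mL outcome, because the article supports equivalence only to 1000 mL. In the 4.5% scenario about half of the transfused women truly lost 1500 mL or less.
5. Confirm that the timing of transfusion relative to the blood sample is recorded. The article mentions transfusion incidence and units, but not this.

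The cost is a few sentences, slightly more analysis work, and outcomes that become partly composite. No change to the sample size is needed.
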